#### Effect evaluation

The primary outcome variable "cumulative recurrent sickness absence days during follow-up" will be compared between the intervention and control group in the multilevel regression analyses. Time until a relapse of sickness absence will be examined by using Cox proportional hazard analysis to estimate hazard ratio's for a relapse and the 95% confidence interval. In case no software is available to conduct these analyses in a multilevel structure, cluster level survival analyses will be conducted with means for each cluster. In these analyses, cluster size will be introduced as a weighting factor. To investigate differences between the intervention and control group in changes (improvement) on all secondary outcomes, multilevel longitudinal analysis will be used. Pre-planned subgroup analyses on type of CMD, line manager participation in the study, size of the company, perceived decision latitude, type of work, and expectancy to stay-at-work will be conducted.

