**Methods/Design:**

The study is designed as a cluster-randomised controlled trial with randomisation at the level of the occupational physician. Employees who have returned to work after a period of sickness absence because of a common mental disorder are included in the study. Employees in the intervention group will receive the SHARP-at work intervention. The intervention focusses on active guidance of employees by occupational physicians during the first weeks of work after sickness absence. Employees in the control group will receive care as usual. Outcomes will be assessed at baseline and at 3, 6, and 12 months follow-up. The primary outcome is cumulative recurrent sickness absence days. Secondary outcome measures are mental health, work functioning, and coping. Adherence to the protocol, communication between stakeholders, and satisfaction with the treatment are the process measures assessed in both study groups. Cost-benefit is calculated from a societal perspective. Finally, prognostic factors for a relapse of sickness absence are investigated.

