### Sample size

For the power calculation, recurrent sickness absence days are considered the primary outcome measure. To calculate the sample size, administrative data from the sickness absence registry of the OHS was used. From 2001 to 2007, recurrent sickness absence days among employees, who had returned to work after a period of sickness absence because of CMDs, were registered. For the power calculation, only recurrent sickness absence days of the first recurrence episode until 1 year later were used to approximate the 1 year follow-up of the present study (N = 4443). The variance in recurrent sickness absence days at the level of the OP was taken into account.

During the above-mentioned period, the mean days of recurrent sickness absence was 68.5 (standard deviation is 119.6). The target of the present study is to reduce the recurrent sickness absence days with 20%, i.e. an average of 12.7 recurrent sickness absence days per employee per year. The OPs in this OHS's dataset were randomly divided into two groups. One group was called "the intervention group" from which 20% of the recurrent sickness absence days was subtracted to create the difference between the intervention and control group and to calculate an effect size.

For a decrease of 12.7 recurrent sickness absence days per employee during 1 year at alpha = 0.05 and ICC = 0.05, 50 OPs, each providing five employees, need to be included in each group (the intervention and control group) [29]. The five employees must be viewed as the average number per OP. For this multilevel power calculation, an effect size of 0.18 was taken into account. This effect size was calculated by using a logtransformation on the data to create a normal distribution and subsequently by dividing the difference in mean days of recurrent sickness absence between the intervention and control group (difference is 0.25) by the standard deviation (standard deviation of difference is 1.4). To include the effect size in the multilevel power calculation, it had to be transformed to a correlation coefficient, which resulted in a correlation of 0.09 [30].

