### Statistical analyses

Due to the multilevel design of the study (i.e. employees are nested in OPs), multilevel regression analyses will be performed according to the intention-to-treat principle. Per protocol analyses will be conducted to explore if deviations from the protocol have caused bias. Descriptive statistics will be used to measure differences in baseline characteristics between the intervention and control group. In case of significant differences, these will be controlled for in the effect evaluations.

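### With secondary outcomes framed as change, the only stated baseline adjustment depends on a significance test, which can cost precision and leave smaller imbalances uncorrected

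*Protocol article*

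**What the plan says.** Three statements in the protocol article bear on this point.

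- The Abstract (Methods/Design) gives the schedule, "Outcomes will be assessed at baseline and at 3, 6, and 12 months follow-up", and the domains, "Secondary outcome measures are mental health, work functioning, and coping". The sections on mental health problems and coping behaviour name the 4DSQ (four scales), the HADS (two) and the UCL (five), which makes 11 scales.
- Effect evaluation gives the secondary analysis: "To investigate differences between the intervention and control group in changes (improvement) on all secondary outcomes, multilevel longitudinal analysis will be used".
- Statistical analyses, which introduces Effect evaluation, gives the covariate rule: "Descriptive statistics will be used to measure differences in baseline characteristics between the intervention and control group", followed by "In case of significant differences, these will be controlled for in the effect evaluations".

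The article does not say whether the baseline score is one of the modelled outcomes, a covariate, or a value constrained to be equal in the two arms. Nowhere does it commit to adjusting for a scale's baseline score regardless of a test. The WRFQ is left out of this point, because its starting value in employees who are only about to return to work is a separate question.

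**The concern.** A baseline score usually predicts the later score on the same scale. Its value as a covariate comes from that correlation, not from whether the arms happen to differ significantly at the start. Tying adjustment to a significance test therefore gives up precision in most trials. It corrects only the largest gaps, and it makes the model depend on the data.

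A comparison of raw change does not repair this. Subtracting the whole baseline score over-corrects whenever rho is below 1, so an arm that starts worse tends to show more improvement without any effect of the intervention.

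The conclusions on mental health and coping, both named as secondary aims, are at stake. The primary outcome is counted after return to work, has no baseline score, and is not affected.

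**Working it through.** **Inputs from the article.** Sample size gives the design: "at alpha = 0.05 and ICC = 0.05, 50 OPs, each providing five employees, need to be included in each group". That is 250 employees per arm and 500 in total, with design effect 1 + (5 - 1) x 0.05 = 1.2. The ICC is stated for recurrent sickness absence days, and using it for the scale scores is an assumption.

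**The plan's own figure.** No precision, power or effect figure is given for any secondary outcome, so there is none to reproduce. The planned effect size concerns the primary outcome (0.25/1.4 = 0.179, given as 0.18). Nothing below uses it.

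**Assumptions.** rho is 0.3, 0.5 or 0.7, since the article gives no value. Variances are equal at all visits, the correlation between any two visits is equal, and there is no dropout.

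**Step 1: precision at one follow-up visit.** In units of the score variance, the arm contrast has variance proportional to:
- change score: 2(1 - rho)
- baseline-adjusted: 1 - rho²

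The ratio of change to adjusted is 2/(1 + rho). The share of precision lost is 1 - (1 + rho)/2 = (1 - rho)/2.

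**Step 2: mean of the three follow-up visits.**
- change: (1 + 2rho)/3 + 1 - 2rho = (4/3)(1 - rho)
- adjusted: (1 + 2rho)/3 - rho²

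The share lost is 0.75(1 - rho).

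**Step 3: the conditional rule.** A simulation (50 OPs x 5 employees per arm, ICC 0.05, 4,000 runs per rho, one follow-up) compared three analyses: pure change, always adjusted, and adjusted only if the baseline gap is significant at 5%.

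| Precision lost against always adjusting | rho 0.3 | rho 0.5 | rho 0.7 |
|---|---|---|---|
| One visit, pure change, formula | 35% | 25% | 15% |
| One visit, pure change, simulated | 33% | 26% | 17% |
| One visit, conditional rule, simulated | 26% | 20% | 13% |
| Mean of three visits, pure change, formula | 52.5% | 37.5% | 22.5% |

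By the one-visit formula, 500 employees analysed as pure change are worth 500 x (1 + rho)/2 = 325, 375 or 425 analysed with baseline as covariate. The conditional rule was not simulated for the three-visit mean.

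**Step 4: does a mixed model avoid the loss by itself?** One data set (rho 0.5, 250 per arm, three follow-ups, no OP clustering) was fitted in two ways. With free arm means at baseline, the group-by-time estimate was 0.0713 (SE 0.075), identical to the difference in raw change. With baseline means constrained equal, the SE was 0.059, which is 37% less variance and agrees with Step 2. The loss therefore depends on how baseline is handled, not on whether the model is longitudinal.

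**Step 5: shift given an imbalance.** If the arms differ by d at baseline, the expected change contrast with no effect is -(1 - rho)d.
- SD of a chance gap: 2 x sqrt(1.2/500) = 0.098 SD.
- Largest non-significant gap: 1.96 x 0.098 = 0.19 SD.
- Shift at that limit: 0.13, 0.10 and 0.06 SD for rho 0.3, 0.5 and 0.7.
- A gap of 0.15 SD at rho 0.5: 0.5 x 0.15 = 0.075 SD.

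**Step 6: average bias.** Over all simulated trials, the mean change contrast with no effect was within 0.002 SD of zero at every rho.

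**The case against.** The strongest objection is that the article does not fix the model. A reader might infer that it commits to change scores, but its wording does not support that. Multilevel longitudinal analysis also covers models with baseline as covariate or with baseline means constrained equal, and under those the loss is zero. A condensed article may leave such detail to a fuller plan. The covariate rule speaks of baseline characteristics and neither names nor excludes the outcome scores. All of this stands, and it is why the point is conditional. It does not remove the point. The article states a covariate rule rather than staying silent, that rule depends on a test, and the stated target is change.

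Three further inferences are tempting but not supported.

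- **Biased results.** A reader might infer that regression to the mean biases the comparison. It acts on both arms alike and gives no bias on average (Step 6). The shift arises only given an imbalance. By chance alone, a gap of at least 0.15 SD that is still non-significant occurs in about 8% of trials per scale.
- **One wide loss range.** Joining the low end for one visit to the high end for the three-visit mean would mix two estimands. It would also ignore that the conditional rule recovers part of the loss.
- **Comparison with 0.18.** Setting 0.075 SD beside the planned effect size is not meaningful. That figure belongs to log-transformed sickness absence days, and no effect is planned for the 4DSQ, HADS or UCL.

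Finally, the efficiency argument treats baseline gaps as chance. OPs know their allocation and invite employees after randomisation (Blinding), and the article concedes that selection by OPs cannot be excluded (Methodological considerations). It describes this for both groups, so selection that differs by arm is plausible but not shown. If gaps are systematic, choosing between change and covariate adjustment is less clear-cut, and neither guarantees removal of selection bias.

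**Conclusion.** The point holds in conditional form, for secondary outcomes only. The stated rule is inferior to always adjusting. If the analysis is carried out as change scores or an unconstrained group-by-time comparison, the loss at one visit is about 13-26% of precision with the conditional rule, or 15-35% without it, for assumed rho from 0.7 to 0.3. For the mean of three visits the pure-change loss is 22.5-52.5% over the same range. If the fuller plan already has baseline as a covariate or constrains it equal, the loss is zero.

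Baseline gaps up to about 0.19 SD would pass the test uncorrected and shift the contrast by about (1 - rho) times the gap. These figures rest on the assumed rho, equal variances and correlations, complete data, and an ICC borrowed from the primary outcome. The change is worth making because the baseline scores are already collected and the rule would otherwise choose the model after seeing the data.

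**What to change.** In Statistical analyses and Effect evaluation, replace the comparison of changes for these scales, and exempt their baseline scores from the significance rule. Suggested wording: each 4DSQ, HADS and UCL scale at 3, 6 and 12 months will be compared between arms in one multilevel longitudinal model (visits within employees within OPs) that always includes that scale's baseline score and the baseline-by-visit interaction as covariates, regardless of any test of baseline differences.

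If a fuller plan already specifies this, the article's wording need only be aligned with it. The cost is a sentence or two, settled before the outcome data are analysed by arm. No new data or measurements are needed. The report should still discuss selection by OPs as a limitation, since adjustment cannot be relied on to remove it.

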#### Treatment of participants in the intervention group

The intervention consists of five steps the employee has to undertake when return-to-work is started. The OP monitors that the employee follows these steps and uses interventions to activate the employee when needed. The five steps are delineated below.

1. Make an inventory of problems and/or opportunities encountered at work

2. Brainstorm on solutions

3. Write down the solutions and the support needed and assess the applicability

4. Discuss the solutions with the line manager and make an action plan

5. Evaluate the action plan and the implementation of solutions

The OP can use assignments for the employee to write down and structure the process. In general, the OP will counsel on the process level. (S)he does not discuss the content of problems and solutions but challenges the employee to reflect on the relative seriousness of problems and the feasibility of solutions. This can be done by asking questions that stimulate the employee to think about possible perspectives. This form of guidance is related to Socratic questioning. The intervention differs from the guideline of the Netherlands Society of Occupational Medicine by the emphasis on problems and possibilities encountered *at work *when an employee has already returned to work.

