#### Treatment of participants in the control group

CAU is delivered according to the evidence-based guideline of the Netherlands Society of Occupational Medicine [21,22]. CAU comprises guidance in regaining control and activating problem solving when the employee is still on sickness absence and at least one consultation session after return-to-work, addressing relapse prevention.

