### Process evaluation measures

A process evaluation is conducted to examine a) the appraisals, attitudes, and activities of OPs, employees, and line managers in the intervention and control group during the treatment period and b) whether OPs adhere to their protocol. OPs who are trained in the intervention, receive a questionnaire before and after the training to examine the quality of the training and the skills and attitudes of the OPs. For the intervention group, a questionnaire is developed for the OP and the employee at baseline. These questionnaires contain items on readiness for change concerning the intervention. At 3-months follow-up, the employees and the OPs in both the intervention and control group receive a questionnaire about the process of treatment during the first three months of return-to-work. The questions elaborate on what was discussed during the consultations, whether assignments were given, which assignments were made, satisfaction with the treatment, and communication between the employee, OP, and line manager. For the intervention group, a questionnaire is also developed for the line manager. The line manager receives a questionnaire on readiness for change before a meeting takes place with the employee as part of the intervention. At 3-months follow-up, the line manager receives a second questionnaire with the same questions as the questionnaires at 3 months for the employee and the OP.

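### Line manager participation is planned as an effect subgroup, but as described it arises during treatment and in the intervention arm only, so it cannot give a randomised subgroup contrast

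*Protocol article*

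**What the plan says.** The Effect evaluation section lists six subgroup factors, beginning "Pre-planned subgroup analyses on type of CMD, line manager participation in the study, size of the company", and continuing with perceived decision latitude, type of work and expectancy to stay at work. It does not define line manager participation.

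Other sections show where line managers enter the study:

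- Treatment of participants in the intervention group, step 4: "Discuss the solutions with the line manager and make an action plan".
- Process evaluation measures: "For the intervention group, a questionnaire is also developed for the line manager". On timing: "The line manager receives a questionnaire on readiness for change before a meeting takes place with the employee as part of the intervention". Later: "At 3-months follow-up, the line manager receives a second questionnaire".
- The process questionnaire sent in both arms at three months names other recipients: "the employees and the OPs in both the intervention and control group receive a questionnaire about the process of treatment".
- The same section opens with a wider aim, to examine "the appraisals, attitudes, and activities of OPs, employees, and line managers in the intervention and control group".
- Treatment of participants in the control group describes guideline care, including "at least one consultation session after return-to-work, addressing relapse prevention". It mentions no line manager step.
- Prognostic measures lists what is measured at baseline. Company size, decision latitude, social support and expectancy to stay at work are there. Line manager participation is not.

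**The concern.** A subgroup analysis of effect compares the randomised arms within levels of a characteristic. That works when the characteristic is settled before treatment begins, cannot be changed by treatment, and is recorded alike in both arms. Line manager participation, as the article describes it, meets none of these conditions. It develops while the intervention is being delivered, it is part of what the intervention sets out to bring about, and it is recorded in one arm.

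Involving the line manager is also one of the components that the Background presents as central to the intervention. A result labelled as a pre-planned subgroup could be read as evidence that the intervention works better, or works only, when the manager is involved. The contrast could not carry that conclusion. Managers who take part may differ from those who do not, and so may the employees who get as far as step 4. Either difference could affect sickness absence without any contribution from the intervention.

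**Working it through.** The plan gives no figure for this subgroup, so none can be reproduced. The check is mainly textual, followed by an illustration on assumed inputs.

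**1. When is the variable fixed?** Under Procedure, the intervention starts only after the baseline questionnaire is returned. The first line manager questionnaire comes before the employee-manager meeting, and that meeting is part of the intervention. Participation is therefore determined during treatment.

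**2. In which arm does it exist?** The sentence introducing the line manager questionnaire is restricted to the intervention group. The three-month contact is called a second questionnaire, so it follows the first. The both-arms mailing names employees and occupational physicians only. No control-arm contact is described.

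**3. What contrast is left?** Write P and N for the mean outcome of participating and non-participating intervention employees, and C for the mean of all controls. With no control counterpart, the two subgroup effects are P − C and N − C. Their difference is (P − C) − (N − C) = P − N. The control arm cancels. The apparent effect modification is a comparison within the intervention arm between groups that were not formed by randomisation.

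**4. How large could the bias be?** Assume an inert intervention, a proportion p participating, and participants who would in any case have r times the days of non-participants. Setting non-participants to 1, randomisation makes the control mean pr + (1 − p). The apparent ratios are r / (pr + 1 − p) for participating and 1 / (pr + 1 − p) for non-participating. Both p and r are assumptions.

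| p | r | Control mean | Participating | Not participating |
|---|---|---|---|---|
| 0.5 | 1.0 | 1.00 | 1.00 | 1.00 |
| 0.3 | 0.8 | 0.94 | 0.85 | 1.06 |
| 0.5 | 0.8 | 0.90 | 0.89 | 1.11 |
| 0.7 | 0.8 | 0.86 | 0.93 | 1.16 |
| 0.5 | 1.2 | 1.10 | 1.09 | 0.91 |

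The last row shows the reversed sign if managers take part more often in difficult cases.

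**5. Would the bias be visible at this sample size?** A simulation used the article's 50 physicians with five employees each per arm, log-scale standard deviation 1.4 and intracluster correlation 0.05, with no treatment effect and 4,000 runs per setting. The tendency to participate was given an assumed correlation with better prognosis. At 50% participation:

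| Assumed correlation | Ratio, participating | Ratio, not participating | Runs with a false subgroup difference |
|---|---|---|---|
| 0 | 0.99 | 1.00 | 5% |
| 0.1 | 0.90 | 1.12 | 24% |
| 0.2 | 0.81 | 1.25 | 72% |
| 0.3 | 0.72 | 1.39 | 96% |

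At 30% or 70% participation, correlations of 0.1, 0.2 and 0.3 gave 21–23%, 63–65% and about 95%. At correlation 0.2 and 50% participation the spurious log-scale gap is about 0.44, against the difference of 0.25 used under Sample size. In every setting the overall comparison between arms stayed unbiased.

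**The case against.** **Both arms are named.** The aim of the process evaluation covers line managers in the intervention and control group, and the Abstract says communication between stakeholders is assessed in both groups. A reader might infer from the questionnaire sentences that the control cell is empty by design and that the interaction can never be estimated. The documents do not go that far: they describe no control-arm line manager contact, but they also contain a sentence that implies some. This is an inconsistency to reconcile. Settling it in favour of both arms would not rescue the subgroup, because participation would still arise after treatment starts and be influenced by it.

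**The variable is undefined, and an article may leave definitions to the full protocol.** This is fair. Participation could mean holding the step 4 discussion, returning a questionnaire, or a measure built from what employees and physicians in both arms report at three months about communication with the line manager. All three arise after treatment starts, so a fuller definition would not remove the difficulty.

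**Collection after allocation is not in itself a fault.** This is correct. Physicians are randomised before any employee is recruited, so decision latitude and expectancy to stay at work are also collected after allocation. Those are measured at baseline, before the intervention starts. What counts against line manager participation is its dependence on treatment.

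**The harm is assumed.** This stands in part. A reader might infer that the subgroup would show a false benefit of manager involvement even if the intervention did nothing. The documents do not say that employees with participating managers have a better prognosis. The bias could be nil or run the other way.

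**Conclusion.** The point holds as a defect in one of six planned subgroup factors. Under the article's own description, a contrast between arms by line manager participation is either not available or not a randomised comparison. This follows from the text and needs no numerical assumption.

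The size and direction of the bias do not follow from the text. The ratios of 0.89 and 1.11 rest on an assumed 50% participation and an assumed 20% fewer days among participants. Under no association with prognosis the bias is zero, and with 20% more days the ratios become 1.09 and 0.91. The simulation shows only that modest assumed associations would often produce an apparent subgroup difference at this sample size.

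A reader might also infer that the main result is compromised. It is not: the primary comparison of cumulative days does not use this variable, and the planned time-to-relapse, secondary-outcome and economic comparisons do not depend on it either.

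**What to change.** Remove line manager participation from the subgroup list in the Effect evaluation section. Report it as an exploratory process or adherence analysis within the intervention arm, with a stated definition and a plain statement that the comparison is not randomised.

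In Process evaluation measures, reconcile the aim that names line managers in both arms with the questionnaires described for the intervention group only.

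If a manager-related effect modifier is wanted, choose a baseline measure taken in both arms. The social support measure under Prognostic measures is a candidate. The article does not say whether it separates support from the supervisor, so that must be checked first. If the effect among employees whose managers would take part is itself of interest, a principal-stratum analysis could address it, but its assumptions would have to be stated.

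The cost is a small edit to the text and no new data collection. The downside is that one pre-planned subgroup is lost as an analysis of effect.
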